| Unrelated                                              | There is no evidence of any causal relationship.                                                                                                                                                                                                                                                                                                                                                                                                                                                                                                                                                                                                                                                                                                                                                                                                                                                                                                                                                                                                                                                                                                                                                                                                   |              |             |                  |                                                  |                 |                                                                                                                                                                                                                                                                                                          |                 |                                                                                                    |                   |                                                                                                                    |
| Possible                                               | There is some evidence to suggest a causal relationship (e, g. the event occurs within a reasonable time after administration of the trial medication). However, the influence of other factors may have contributed to the event (e.g. the patient’s clinical condition, other concomitant treatments).                                                                                                                                                                                                                                                                                                                                                                                                                                                                                                                                                                                                                                                                                                                                                                                                                                                                                                                                           |              |             |                  |                                                  |                 |                                                                                                                                                                                                                                                                                                          |                 |                                                                                                    |                   |                                                                                                                    |
| Probable                                               | There is evidence to suggest a causal relationship and the influence of other factors is unlikely.                                                                                                                                                                                                                                                                                                                                                                                                                                                                                                                                                                                                                                                                                                                                                                                                                                                                                                                                                                                                                                                                                                                                                 |              |             |                  |                                                  |                 |                                                                                                                                                                                                                                                                                                          |                 |                                                                                                    |                   |                                                                                                                    |
| Definitely                                             | There is clear evidence to suggest a causal relationship and other possible contributing factors can be ruled out.                                                                                                                                                                                                                                                                                                                                                                                                                                                                                                                                                                                                                                                                                                                                                                                                                                                                                                                                                                                                                                                                                                                                 |              |             |                  |                                                  |                 |                                                                                                                                                                                                                                                                                                          |                 |                                                                                                    |                   |                                                                                                                    |
| Unexpected Serious Adverse Reaction (known as a SUSAR) | An Unexpected Serious Adverse Reaction means a serious adverse reaction, the nature and severity or outcome of which is not consistent with the reference safety information (RSI).                                                                                                                                                                                                                                                                                                                                                                                                                                                                                                                                                                                                                                                                                                                                                                                                                                                                                                                                                                                                                                                                |              |             |                  |                                                  |                 |                                                                                                                                                                                                                                                                                                          |                 |                                                                                                    |                   |                                                                                                                    |

As some study related screening procedures are non-routine and potentially invasive, the risk of Adverse Events (AEs) and Serious Adverse Events (SAEs) occurring after consent to participate in the trial and before starting trial treatment, has been assessed as high. Therefore, these definitions apply to all trial participants from consent until day 60.

**N.B:** To avoid confusion or misunderstanding of the difference between the terms “serious” and “severe”, the following note of clarification is provided: “Severe” is often used to describe intensity of a specific event, which may be of relatively minor medical significance. “Seriousness” is the regulatory definition supplied above.

## **6.1.2 Detecting, Recording and Reporting of Adverse Events**

### **6.1.2.1 Detection of Adverse Events**

Participants will be asked at each trial visit about the occurrence of AEs since their last visit.

AEs will be recorded, notified, assessed, reported, analysed and managed in accordance with the Medicines for Human Use (Clinical Trials) Regulations 2004 (as amended) and the trial protocol.

AEs must be recorded as they are reported, whether spontaneously volunteered or in response to questioning about well-being at trial visits. The questioning about AEs will cover the current visit as well as the period between the previous and the current visit. All AEs must be documented in full in the patient's medical records whether they are required to be recorded in the CRF or not.

### **6.1.2.2 Recording of Adverse Events**

Full details of AEs including the nature of the event, including the event term, start and stop dates, severity, seriousness and causality (relationship of the AE to each trial IMP) and outcome will be recorded in the patient's medical records. All AEs must be reported from the start of treatment and followed until:

- They resolve
- If present at pre-treatment, until the AE returns to the level observed at that time
- The AE is confirmed as unlikely to ever resolve

If none of the criteria above are met by follow-up day 29, the AE no longer requires to be followed up. Perceived lack of efficacy is not an AE.

An exacerbation of a pre-existing condition is an AE.

The Investigator does not need to actively monitor patients for AEs once the trial has ended, unless required.

Adverse events occurring in the period between consent and randomisation do not require to be recorded in the CRF if they are unrelated to any study specific screening procedure.

## **6.1.3 Assessment of Adverse Events**

AEs must be assessed for seriousness, causality and severity. This assessment is the responsibility of the PI (or designee).

In determining whether an AE is an adverse reaction, Investigators must consider if there is a reasonable possibility of establishing a causal relationship between the event and favipiravir based on their analysis of all the available evidence. The assessment must be made on the basis of

anticipated pharmacological properties of favipiravir as specified in the IB or related to the patient's disease, either the disease under investigations or a concurrent illness.

The investigator must, whenever possible, provide a causality assessment for AEs based on the information available at reporting and their knowledge of the disease and favipiravir. The causality assessment provided by an Investigator shall not be downgraded by the CI.

| Relationship | Description                                                                                                                                                                                                                                                                                       |
|---------------------|----------------------------------------------------------------------------------------------------------------------------------------------------------------------------------------------------------------------------------------------------------------------------------------------------------|
| Unrelated    | There is no evidence of any causal relationship.                                                                                                                                                                                                                                                         |
| Possible     | There is some evidence to suggest a causal relationship (e, g. the event occurs within a reasonable time after administration of the trial medication). However, the influence of other factors may have contributed to the event (e.g. the patient's clinical condition, other concomitant treatments). |
| Probable     | There is evidence to suggest a causal relationship and the influence of other factors is unlikely.                                                                                                                                                                                                       |
| Definitely   | There is clear evidence to suggest a causal relationship and other possible contributing factors can be ruled out.                                                                                                                                                                                       |

#### **6.1.4 Reporting of a Serious Adverse Event**

Investigators must report all Serious Adverse Events (SAEs) to the Pharmacovigilance Office, CRUK CTU immediately and under no circumstances should this exceed 24 hours following first awareness of the event by the Investigator or site staff.

In addition, all incidences of AT (ALT or AST) elevation > 3 times upper limit of normal (ULN) are classed as adverse events of special interest and should be reported as SAEs within the timeframe stated above.

The following events are excluded from reporting as SAEs

- Elective hospitalisations
- Day case admissions for treatment of underlying disease
- A and E attendance for an event that is not immediately life threatening and does not result in admission

Serious Adverse Events occurring in the period between consent and randomisation do not require to be reported if they are unrelated to any study specific screening procedure.

SAEs can be reported via the following means:

Pharmacovigilance [contact]

Email: [[contact]](mailto:[contact])

For any guidance on SAE reporting please contact the Pharmacovigilance team on the following numbers:

[contact] or [name]

The purpose of this obligation is to ensure the CI on behalf of the Sponsor, has the necessary information to continuously assess the benefit-risk balance of the clinical trial.

For guidance on submitting and completing the initial and follow up SAE report forms please refer to the SAE report form Completion Guidelines, which will be provided by the Pharmacovigilance Office, CRUK CTU, Glasgow.

The CI will receive notification, by email, of all SAEs received.

SAEs must be reported locally by the PI at each site in accordance with the local practice at their site (i.e. R&D Office).

A follow-up report must be submitted when the SAE resolves, is unlikely to change, or as soon as additional information becomes available. If the SAE is a potential SUSAR then follow up information must be provided as quickly as possible and in the timeframe requested by the CRUK CTU and CI. All follow-up information is required to be reported promptly and follow up reports submitted until all AEs listed on the initial SAE report resolve. A follow-up report must be submitted if additional AEs listed on the initial SAE report have resolved or will never resolve. A follow-up report should also be submitted if additional AEs occur or new information becomes available about previously reported AEs.

All SAEs are required to be reported from start of treatment and for up to follow-up day 60. Any event that meets the criteria of a SAE (including events that the Investigator thinks are medically significant but maybe do not require hospitalisation or are fatal etc.) that occur after day 60 follow-up are also required to be reported if the Investigator thinks that the SAE is related to protocol treatment. Such SAEs must be reported to the Pharmacovigilance office without undue delay.

For any questions relating to SAE reporting, please contact the Pharmacovigilance team:

Email: [[contact]](mailto:[contact])

[contact] or [name]

Contact details are also provided at the front of the protocol and in the SAE report form completion guidelines.

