| Serious Adverse Event (SAE) | 
A serious adverse event (SAE) means any untoward medical occurrence that at any dose requires the following, whether or not considered related to the trial treatment.
 

• Requires inpatient hospitalisation or prolongation of existing hospitalisation*

• Results in persistent or significant disability or incapacity

• Results in a congenital anomaly/birth defect

• Is life threatening (i.e. at the time of the event)**

• Or results in death

• Is considered medically significant by the Investigator***

 
*Requires in-patient hospitalisation should be defined as a hospital admission required for treatment of an AE. No time frame is specified for the duration of the admission.
 
**Life threatening means that the patient was at immediate risk of death from the event as it occurred. It does not include an event that, had it occurred in a more serious form, might have caused death.
 
***Considered medically significant by the Investigator are events that may not result in death, are not life threatening, or do not require hospitalisation, but may be considered a serious adverse experience when, based upon appropriate medical judgement, the event may jeopardise the patient and may require medical or surgical intervention to prevent one of the outcomes listed above.
 |

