#### **7.1.5 Safety**

The worst toxicity grades (including AEs of special interest) experienced during active treatment will be compared between the study arms using the Mann-Whitney U test. P-values will be interpreted in the context of the multiple tests performed. This analysis will be restricted to events that occur in more than 10% of patients in either arm.

All Serious Adverse Events (including SARs and SUSARs) will be tabulated.

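### The A&E exclusion in Protocol 6.1.4 tells sites not to report some events that 6.1.1 defines as serious, because it makes no exception for medically significant events

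*Protocol*

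**What the plan says.** Protocol section 6.1.1 lists the criteria that make an event serious. One of them, separate from hospitalisation and from threat to life, is that the event "Is considered medically significant by the Investigator". The footnote says these are "events that may not result in death, are not life threatening, or do not require hospitalisation, but may be considered a serious adverse experience", and that they "may require medical or surgical intervention to prevent one of the outcomes listed above".

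Section 6.1.4 opens with the duty to report: "Investigators must report all Serious Adverse Events (SAEs) to the Pharmacovigilance Office, CRUK CTU immediately", and never later than 24 hours after the site first becomes aware. A later paragraph of 6.1.4 repeats the duty for all SAEs from the start of treatment to day 60.

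Between these two statements stands a list of three kinds of event excluded from SAE reporting: elective hospital stays, day-case admissions for the underlying disease, and "A and E attendance for an event that is not immediately life threatening and does not result in admission".

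Under section 6.1.5, the Pharmacovigilance Office and the Chief Investigator assess the expectedness of SAEs against the reference safety information in force when the SAE is received. For the analysis, section 7.1.5 says: "All Serious Adverse Events (including SARs and SUSARs) will be tabulated".

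**The concern.** The A&E item applies when two conditions hold: no immediate danger to life, and no admission. The 6.1.1 footnote says that these same two features do not stop an event from being serious. A site can therefore find that one section calls an event an SAE and another tells it not to send the form.

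What is at stake is expedited safety information. Outpatients take favipiravir at home, are assessed by telephone on days 1 to 10 and have no routine blood tests scheduled between screening and day 15. A&E is a plausible place for an acute reaction to be treated. Section 5.7.2 says that the adverse reactions noted in US and Japanese studies came from lower doses and shorter treatment than in this protocol, so the route for unexpected serious reactions matters here. Section 6.1.4 itself gives the purpose of SAE reporting as keeping the benefit-risk balance under continuous review.

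**Working it through.** No arithmetic decides this point. The check takes one event through each rule in turn.

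**Test event.** A participant between the start of treatment and day 60 has an acute event. It is treated in A&E, poses no immediate threat to life, and the participant goes home. The investigator judges it medically significant because treatment was needed to prevent something worse.

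1. **Is it serious (6.1.1)?** Yes. Medical significance is sufficient alone, and the footnote covers events without threat to life or hospitalisation that need intervention.
2. **Must it be reported (opening of 6.1.4)?** Yes. The duty covers all SAEs, within 24 hours.
3. **Does the reporting window cover it (later in 6.1.4)?** Yes. All SAEs up to day 60 are included.
4. **Does the exclusion list cover it (6.1.4)?** Yes. Both conditions of the A&E item are met and nothing restores an event that is serious on another ground.

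Steps 2 and 3 say report; step 4 says do not. The protocol does not say which prevails.

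**Consequences if a site follows the list**

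- *24-hour reporting.* Lost directly.
- *SUSAR assessment (6.1.5).* Lost in practice, because the assessment starts from an SAE that has been received.
- *SAE table (7.1.5).* Conditional. The section promises a table of all SAEs. The event is missing only if the table is built from reported SAEs, which the protocol does not state.
- *Comparison of worst toxicity grades (7.1.5).* This is only a partial backstop. It is restricted to events in more than 10% of patients in either arm; with 151 per arm, 0.10 × 151 = 15.1, so at least 16 patients. A rarer event type does not enter it.

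**What still captures the event**

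- Section 6.1.2.2 requires it to be recorded as an adverse event in the medical records, with severity, seriousness and causality.
- Section 6.1.3 requires the investigator to assess seriousness.
- ALT or AST above 3 times the upper limit of normal has its own SAE reporting rule in 6.1.4.
- Section 6.1.7 provides for regulatory reporting of other unexpected events that might materially change the risk-benefit assessment.

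**Size.** The protocol gives no rate of A&E attendance, or of medically significant events managed without admission. The number affected cannot be derived from it.

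**The case against.** The strongest reply is that the list only clarifies the hospitalisation criterion. All three items are kinds of hospital contact, so the natural purpose is to say that such contact does not in itself make an event serious. The duty to report all SAEs, stated before and after the list, fits that reading, and the SAE completion guidelines, which are not shown, may say so.

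This is a plausible account of the intent, but not of the text. The list is in the reporting section, not under the hospitalisation footnote, and it removes events from SAE reporting outright. The A&E item also makes its own exception for immediate threat to life, a separate seriousness criterion. A pure clarification of hospitalisation would not need that exception, and naming only this one invites the reading that no other criterion counts.

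The reply that these events are not wholly lost stands, for the reasons listed in the working.

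A reader might infer more than the documents support:

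- *That the day-case item has the same fault.* Section 6.1.1 says of admissions that "No time frame is specified for the duration of the admission", but it refers to admissions needed to treat an adverse event. The day-case item is limited to treatment of the underlying disease, so there is no clear conflict.
- *That late events are handled more strictly than events during treatment.* The rule for events after day 60 describes them as "including events that the Investigator thinks are medically significant but maybe do not require hospitalisation". That duty is limited to events thought related to treatment, so it is narrower, and nothing says the exclusion list lapses at day 60.
- *That the loss falls on the favipiravir arm.* The exclusion applies to both arms alike. An uneven loss would need an excess of such events caused by the drug, and the protocol gives no figure for that.

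**Conclusion.** The inconsistency is real and is in the current text. For a medically significant event treated in A&E without admission, 6.1.1 and the general duty in 6.1.4 require an SAE report, while the exclusion list in 6.1.4 forbids one. On the literal reading, the loss of 24-hour reporting is certain and the loss of SUSAR assessment follows from it. Absence from the SAE table is an inference that depends on the source of the table.

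The point touches no efficacy endpoint, sample size or error rate. A reader might be tempted to attach an event count, but any count would rest on a rate that the protocol does not supply. The conclusion assumes that sites apply the list as written and that the completion guidelines do not already correct it. It is worth fixing because it concerns an expedited safety rule and the change is very small. Sites also need a clear instruction: section 10.3 says that systematic or persistent violations, including late SAE reporting, may be deemed a serious breach.

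**What to change.** Reconcile 6.1.1 with both statements of the reporting duty in 6.1.4 by adding one clause to the exclusion list. It should say that the listed exclusions apply only to the hospitalisation criterion, and that an event meeting any other seriousness criterion in 6.1.1, including medical significance in the investigator's judgement, must still be reported as an SAE. Put the same sentence in the SAE completion guidelines. The three listed items can otherwise stay as they are.

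The cost is one clause in each of the two documents and a few more SAE forms. No visit, assessment or analysis changes.
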